### Limitations of the Trial

As described above, the proposed trial has the potential to prevent patients with mild COVID-19 from developing a more severe illness, but there will be some limitations to this trial. First, for subjects receiving standard treatments for COVID-19 that will not be withheld as part of the trial, it may be difficult to disentangle the effectiveness of convalescent plasma therapy on the outcomes of subjects from one of the standard treatments. Second, although the number of persons vaccinated against SARS-CoV-2 has increased in Japan, the potential for beneficial effects of convalescent plasma therapy for vaccinated subjects remains unknown. In this trial, subjects vaccinated against SARS-CoV-2 will be excluded; therefore, the number of subjects who could take part in the trial will decrease over time. Third, casirivimab/imdevimab and sotrovimab, which are anti-SARS-CoV-2 monoclonal antibody treatments, and molnupiravir, an antiviral drug, were approved in Japan from July to December 2021 to prevent the development of symptomatic COVID-19, approximately 5–10 months after the first patient enrolled in this trial in February 2021. Because the target population groups of casirivimab/imdevimab, sotrovimab, and molnupiravir therapy overlap with that of this trial, this could cause difficulties when enrolling subjects. Taking these limitations into consideration and closely observing the developing trends of novel drugs and therapies, issues regarding subject enrollment should be reconsidered in the future. Nonetheless, improvements shown by our trial may lead to the expansion of the use of convalescent plasma therapy.

## Figures and Tables

**Table 1 life-12-00856-t001:** Secondary endpoints of the trial.

Objective	Endpoint	Rationale for the Endpoint
Prevention of mechanical ventilation or death.	Use of mechanical ventilation or death by days 14 and 28.	Prognosis is an endpoint that is not subjective.
Prevention of death.	Mortality on days 14 and 28.	Prognosis is an endpoint that is not subjective.
Prevention of the need for supplemental oxygen use.	Percentage of subjects who used oxygen on days 3, 5, 7, 14, and 28.	It is an endpoint that is not subjective.
To assess the shortening of the duration of symptoms (the time to clinical improvement).	Clinical improvement is defined as the first day a subject meets one of the three categories on the ordinal scale shown below: Not requiring hospitalization or supplemental oxygen and not requiring continuation of treatment. No hospitalization is needed but requires the limitation of activities and/or oxygen therapy at home. No hospitalization and no limitation of activities.	Clinical improvement is related to efficacy.
To assess clinical improvement on days 3, 5, 7, 14, and 28 in subjects given the convalescent plasma.	Clinical improvement on days 3, 5, 7, 14, and 28 (on an 8-point scale)	Clinical improvement is related to efficacy.
Time to improvement on the National Early Warning Score, UK (NEWS)	Time to discharge from the hospital or the maintenance of NEWS ≤2 for 24 h (whichever occurs first) NEWS on days 3, 5, 7, 14, and 28.	Clinical improvement is related to efficacy.
Decrease in the viral load in the convalescent plasma group after convalescent plasma transfusion.	Time-weighted average change and the numerical change in the SARS-CoV-2 virus load in nasopharyngeal swabs from day 0 to each day of assessment.	Change in the viral load has been used as the index of the therapeutic effect in many studies.
To assess safety after convalescent plasma transfusion.	Occurrence of adverse events.	It is necessary to evaluate safety.
To screen and identify variants.	Determine if variants are present in nasopharyngeal swab samples on day 0	Variants are related to efficacy because it has been reported that variants may reduce the antiviral activity of neutralizing antibodies.

**Table 2 life-12-00856-t002:** Study schedule.

Activities	Admission		Day 0 (Day of Transfusion) ^i^		Day 1 (1 d after Transfusion)	Day 3 (3 d after Transfusion)	Day 5 (5 d after Transfusion)	Day 7 (7 d after Transfusion)	Day 14 (14 d after Transfusion)	Day 21 (21 d after Transfusion)	Day 28 (28 d after Transfusion)	Day 90 (90 d after Transfusion)	Discontinuation of the Study
			Before Trans- Fusion	3 h after Start of Trans-Fusion ^j^									
Acceptable time window ^a^	−3 to 0		Reference day		+1	±1	±1	±1	±3	±3	±3	+30	–
Informed consent	X												
Confirmation of eligibility		X ^k^											
Registration and randomization of a subject		X											
Characteristics of a subject		X ^k^											
Plasma transfusion ^h^			X		X ^b^								
Vital signs ^d^ and clinical condition ^c^			X	X ^h^	Once daily during hospitalization and days 3, 5, 7, 14, 21, and 28 after discharge								X
Physical findings ^d^		X ^k^	X	X ^h^	X	X	X	X	X	X	X		X
Pregnancy test ^l^		X ^k^											
Collection of swabs (2 sticks) ^m^			X		X	X	X	X	X	X	X		X ^e^
Blood test (biochemistry, complete blood count, and coagulation) ^m^		X ^k^			X	X	X	X	X	X	X		
Blood test (blood type)		X ^k^											
Blood test (cross-match) ^h^		X											
Blood test (infection screening) ^f^		X ^k^											
Blood test (post-transfusion infection test) ^g,h^												X	
Storage of plasma ^m^			X		X	X	X	X	X	X	X		
Storage of serum ^m^			X		X	X	X	X	X	X	X		
Radiography (chest X-ray)		X ^k^											
Concomitant drugs ^c^			X		Every day during hospitalization and days 3, 5, 7, 14, 21, and 28 after discharge								X
Adverse events ^c^				X ^h^	Every day during hospitalization and days 3, 5, 7, 14, 21, and 28 after discharge							X ^h^	X

^a^ If the days overlap because of the acceptable time window, it is not allowed to collect the data for 2 d on the same day (e.g., it is not allowed to collect the data for both day 1 and day 3 on day 2). ^b^ When Grade C plasma is used, it will be infused on day 1. ^c^ When a subject has been discharged, the data can be collected by phone on or after day 7. ^d^ When a subject has been discharged, it is allowed to not collect data on or after day 7. ^e^ This should be performed if a subject discontinues the study on and before day 14. ^f^ Similar to tests for infectious diseases conducted at registration, HBsAg, HBsAb, HCVAb, HIV-1/2Ab, Syphilis-RPR/TPHA, and HTLV-1 Ab should be measured. ^g^ Similar to the post-transfusion infection test, HBV-DNA quantification, HCV core protein, and HIV-1/2Ab assays should be performed (the test should also be performed in a subject who has stopped transfusion prematurely). ^h^ These data will be collected in the convalescent plasma group. ^i^ The date of transfusion scheduled at the time of randomization is day 0 in both the convalescent plasma group and the standard of care group. ^j^ When Grade C plasma is used, the data to be collected 3 h after the start of transfusion on day 0 should be collected both on days of first and second transfusions. ^k^ The results of the tests as the regular practice before informed consent can be used. ^l^ It is performed in premenopausal female subjects. ^m^ When a subject has been discharged, it is allowed to not collect samples on or after day 14.

**Table 3 life-12-00856-t003:** Laboratory tests performed as part of the trial.

Hematology	Hemoglobin, Hematocrit, White Blood Cell Count with Differential, and Platelet Count
Coagulation	APTT, PT-INR, and D-Dimer
Blood biochemistry	Albumin, AST, ALT, bilirubin, CRP, blood glucose, urea nitrogen, creatinine, LDH, creatine kinase, potassium, and sodium
Infection screening	HBsAg, HBsAb, HCVAb, HIV-1/2Ab, Syphilis-RPR/TPHA, and HTLV-1Ab.
Pregnancy test	Urine or blood (HCG)
Blood type and cross-match	Blood type: A/O/B/AB, Rh +/−; cross-match: compatible/incompatible
SARS-CoV-2 viral load	Nasopharyngeal swabs
Samples for storage	Serum (1.5 mL) and plasma (1.5 mL)
Post-transfusion infection test	HBV-DNA quantification, HCV core protein, and HIV-1/2Ab

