### 2.10. Participation and Follow-Up Periods

The subjects in both the convalescent plasma and standard of care groups will be followed up for up to 28 d to detect any adverse events. In addition, the convalescent plasma group will be examined for post-transfusion infections on day 90. The observation period for the trial will run from the day of registration of the first subject until 31 March 2022 (scheduled).

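### For discharged subjects, the ±3-day window lets the day-28 status call fall on days 25–27, so a death or ventilation between that call and day 28 may go unobserved, and only the plasma arm has a later scheduled contact

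*Protocol article*

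**What the plan says.** The endpoints are in Table 1 of the protocol article. One is cumulative: "Use of mechanical ventilation or death by days 14 and 28". The other is "Mortality on days 14 and 28".

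Table 2 sets the data collection. Its row headed "Acceptable time window" gives ±3 days for the day 14, 21 and 28 contacts. Vital signs and clinical condition are collected "Once daily during hospitalization and days 3, 5, 7, 14, 21, and 28 after discharge". I read the listed days as study days for subjects who have left hospital, because every column of Table 2 counts from day 0 and section 2.10 follows both arms for up to 28 days.

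Footnote c of Table 2 adds: "When a subject has been discharged, the data can be collected by phone on or after day 7". Footnotes d and m allow vital signs, physical findings and samples to be skipped after discharge, from day 7 and day 14 respectively. A phone call may therefore be the only day-28 evidence for a discharged subject.

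Section 2.10 states that "the convalescent plasma group will be examined for post-transfusion infections on day 90". In Table 2 the day-90 infection test and adverse-event entry carry footnote h, which restricts them to the plasma group. Clinical condition is not collected at day 90.

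**The concern.** An endpoint that runs to day 28 needs status known on or after day 28. For a discharged subject, the schedule accepts a last status from day 25, and the article does not require it to be confirmed later. If the subject dies or is ventilated on days 26 to 28, no scheduled contact in the standard-of-care arm would pick this up. In the plasma arm, the day-90 adverse-event contact might.

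Two secondary endpoints are at stake, along with equal ascertainment of them between arms in an open-label trial. Table 1 justifies both endpoints by their objectivity, and that advantage depends on complete capture. This is a data-collection rule that the article itself states, and no later analysis can recover a status that was never collected.

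Day 14 does not have the same problem, because a status taken early there can be completed at the day-21 or day-28 contact.

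**Working it through.** The plan gives no event rate or power for the day-28 endpoints, so there is no figure of its own to reproduce. Its total of 200 (section 2.12), at 1:1 allocation (section 2.4), gives 100 per arm.

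**1. Length of the gap.** The earliest permitted contact is 28 − 3 = day 25.

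| Day of contact | Days unobserved before the end of day 28 | Share of 28 days |
|---|---|---|
| 25 | 3 | 3/28 = 10.7% |
| 26 | 2 | 2/28 = 7.1% |
| 27 | 1 | 1/28 = 3.6% |
| 28 to 31 | 0 | 0% |

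If contacts were spread evenly over days 25 to 31 (an assumption), the mean gap would be (3 + 2 + 1 + 0 + 0 + 0 + 0)/7 = 6/7 day, and (6/7)/28 = 3.1%.

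**2. Who is affected.** Inpatients are recorded daily, so they have no gap. It arises only for a subject who has been discharged and whose day-28 contact falls on days 25 to 27.

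**3. Events that could fall in the gap.** The documents give no 28-day risk r, so I assume a range and a constant hazard h = −ln(1 − r)/28. The probability of a first event after day 25 and by day 28 is exp(−25h) − exp(−28h), which equals (1 − r)^(25/28) − (1 − r).

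| Assumed r | Risk by day 25 | Probability of event in days 26–28 | Per 100 subjects |
|---|---|---|---|
| 1% | 0.00893 | 0.00107 | 0.11 |
| 2% | 0.01788 | 0.00212 | 0.21 |
| 5% | 0.04476 | 0.00524 | 0.52 |
| 10% | 0.08978 | 0.01022 | 1.02 |

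These are ceilings, because they suppose that every subject is discharged and called on day 25. With 100 per arm, the ceiling is about one event per arm at the top of the range and about a tenth of an event at the bottom.

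**4. Later contacts by arm.** Standard of care has none scheduled after day 28. The plasma arm has day 90 (window +30), with an adverse-event entry but no clinical-condition entry. The route by which a late event could surface therefore exists in one arm only.

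**5. After the change.** With a window of 0 to +3, the earliest contact is day 28, and the unobserved part falls from at most 3 days to 0, counted in whole days. The sample size does not change.

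**The case against.** The strongest reply is that this is ordinary scheduling. A symmetric ±3-day window at a four-week contact is common and is the same in both arms. Inpatients are covered daily, and calls on days 28 to 31 cover the whole interval. Section 2.10 states 28 days of adverse-event follow-up in each arm. A death or ventilation might also be reported outside the scheduled calls, under safety rules in Supplementary Information S5, which is not shown. To be missed, an event would have to occur within three days of a call that found the subject alive and out of hospital.

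Most of this stands, and it limits the point to discharged subjects called early. It does not remove the gap: the article sets no requirement to confirm status on or after day 28, and whether another reporting route closes the gap cannot be settled from it.

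A reader might infer more than the documents support:

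- **That the day-28 endpoints as a whole are not observed to day 28.** Daily inpatient recording and contacts from day 28 onward rule this out.
- **That an early call is scored as event-free through day 28.** The article nowhere says so. Handling of last contact belongs to the analysis plan (Supplementary Information S4, not shown).
- **That the comparison is biased against plasma.** This would need day-90 information to be fed back into the day-28 endpoints, which the article does not state. Different ascertainment by arm is possible, but its effect on the result is not established.
- **That oxygen use at day 28 is affected in the same way.** It is a point status, for which a visit window is normal.

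**Conclusion.** The point holds in a limited form. For discharged subjects contacted on days 25 to 27, the article's schedule leaves one to three days unobserved for the ventilation-or-death composite and for day-28 mortality. Only the plasma arm has a later scheduled contact at which such an event could surface, so ascertainment can differ by arm.

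The likely effect is small: the ceiling of about 0.1 to 1 event per 100 subjects rests on assumed 28-day risks of 1% to 10% and a constant hazard. The primary endpoint, viral load to days 3 and 5, is untouched. This is a cheap improvement to a stated data-collection rule and does not correct a contradiction in the plan. It is worth making because totals may be low in subjects who enter with SpO2 of at least 95% on room air, so that a single event could be visible.

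**What to change.** In Table 2, give the day-28 clinical-condition contact (vital status and ventilation) its own window of 0 to +3 days in both arms, and have the caller ask about status through day 28. Swabs and blood can keep ±3.

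This takes one line in the schedule. Phone contact is already permitted, so it need not add a visit. The downside is slightly less flexibility in scheduling the last call.

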## Data Availability

Data are available from the principal investigator on reasonable request.

## Abbreviations

COVID-19	coronavirus disease 2019
ECMO	extracorporeal membrane oxygenation
EDC	Electronic Data Capture
MERS	Middle East respiratory syndrome.
NIH	National Institute of Health
RCTs	randomized controlled trials
SARS	severe acute respiratory syndrome
WHO	World Health Organization
